### Statistical analyses

Two analysis populations will be established: the safety analysis set and the efficacy analysis set. The safety analysis set will include all patients who were allocated, and the numbers and percentages of safety endpoints will be compared between groups by Fisher's exact test.

The subject characteristics collected upon enrollment will be analyzed by intergroup comparisons of continuous variables by analysis of variance and of categorical variables by Fisher's exact test.

The efficacy analysis set will include all patients for whom primary endpoint data are available based on intention-to-treat principle. Using the mixed effects model for repeated measures, we will perform intergroup comparisons of changes in the FMA upper-limb score at 5 and 10 Weeks of the treatment phase. This model will include the group, time point, group-by-time interaction term, baseline FMA upper-limb score, sex, and botulinum toxin injection. For multiplicity adjustment, Dunnett's test will be employed with the RT group used as a reference. The same analysis will be conducted for the secondary outcomes. The level of significance is set at 0.05.

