## Abstract

**Background:** Stroke patients experience chronic hemiparesis in their upper extremities leaving negative effects on quality of life. Robotic therapy is one method to recover arm function, but its research is still in its infancy. Research questions of this study is to investigate how to maximize the benefit of robotic therapy using ReoGo-J for arm hemiplegia in chronic stroke patients.

**Methods:** Design of this study is a multi-center parallel group trial following the prospective, randomized, open-label, blinded endpoint (PROBE) study model. Participants and setting will be 120 chronic stroke patients (over 6 months post-stroke) will be randomly allocated to three different rehabilitation protocols. In this study, the control group will receive 20 min of standard rehabilitation (conventional occupational therapy) and 40 min of self-training (i.e., sanding, placing and stretching). The robotic therapy group will receive 20 min of standard rehabilitation and 40 min of robotic therapy using ReoGo®-J device. The combined therapy group will receive 40 min of robotic therapy and 20 min of constraint-induced movement therapy (protocol to improve upper-limb use in ADL suggests). This study employs the Fugl-Meyer Assessment upper-limb score (primary outcome), other arm function measures and the Stroke Impact Scale score will be measured at baseline, 5 and 10 weeks of the treatment phase. In analysis of this study, we use the mixed effects model for repeated measures to compare changes in outcomes between groups at 5 and 10 Weeks. The registration number of this study is UMIN000022509.

**Conclusions:** This study is a feasible, multi-site randomized controlled trial to examine our hypothesis that combined training protocol could maximize the benefit of robotic therapy and best effective therapeutic strategy for patients with upper-limb hemiparesis.

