## Materials and methods

### Objective

This study is intended to verify the increased efficacy of self-training with robotic therapy compared with the commonly practiced traditional occupational therapy on upper-limb motor function and function in ADL in moderate to severe chronic post-stroke upper-limb hemiplegic patients. In addition, another objective of the study is to verify the degree of superiority of combination training including both robotic therapy and CIMT over training with robotic therapy alone in these patients. Therefore, in this study, primary objective is to compare the RT and control group, secondary objective is to compare the RT and the CT group. Additionally, to compare the CT and control group is auxiliary analysis. We hypothesize that robotic therapy will improve recovery over the usual care alone, and that combining robotic therapy with CIMT will further enhance its benefits.

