### Outcomes

All outcomes will be measured at baseline, 5 and 10 weeks. The primary outcome examined will be changes in the FMA upper-limb score (9). This assessment examines motor and joint function, balance, and sensation in hemiplegic patients and results are represented as a numerical score with a maximum of 66 points.

Secondary outcomes include changes in: (1) the “amount of use” and “quality of movement” components of the MAL-14 scale (11), which assesses limb function in ADL; (2) the individual components of the FMA (9); (3) the ARAT score, another measure of upper-limb function (10); (4) the motricity index (26), an assessment of muscle strength in stroke patients; (5) the MAS score (20), which assesses muscle tone (i.e., spasticity); (6) the active range of motion of the shoulder, elbow, forearm, wrist, and fingers (27); and (7) the Stroke Impact Scale (28), a quality of life assessment scale for stroke patients.

Safety outcomes will include the occurrence of any adverse events. Adverse events will be assessed as either related or unrelated to the study treatment, and their severity graded using the CTCAE Ver 4.03 (29) as a reference. All adverse events will be recorded on the medical chart and case report form. In the case of serious adverse events, including those that are life-threatening or result in hospitalization, a “serious adverse event and malfunction report” will be prepared by the investigator and submitted to the hospital director promptly.

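### The primary FMA outcome has no named time point: groups are compared at weeks 5 and 10 on equal footing, and the plan does not say which visit decides the principal objective

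*Protocol article*

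**What the plan says.** - **Outcome.** The Outcomes section states "The primary outcome examined will be changes in the FMA upper-limb score" and gives the assessment schedule as "All outcomes will be measured at baseline, 5 and 10 weeks". It attaches no visit to the primary outcome.
- **Analysis.** The Statistical analyses section plans a mixed model for repeated measures with a group-by-time term and states "we will perform intergroup comparisons of changes in the FMA upper-limb score at 5 and 10 Weeks of the treatment phase". The abstract likewise plans "to compare changes in outcomes between groups at 5 and 10 Weeks".
- **Multiplicity.** "For multiplicity adjustment, Dunnett's test will be employed with the RT group used as a reference", followed at the end of the section by "The level of significance is set at 0.05".
- **Ranking of arm comparisons.** The Objective section does rank these: "primary objective is to compare the RT and control group, secondary objective is to compare the RT and the CT group". CT versus control is auxiliary.
- **Sample size.** The Sample size section powers RT versus control with a single two-sided t-test at 0.05. It names no visit.

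No section ranks week 5 against week 10, sets a testing order for them, or says whether one visit or both must be significant.

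**The concern.** The arms are ranked but the visits are not. Because the model has a group-by-time term, each contrast with RT can be estimated separately at each visit. That gives two contrasts × two visits = four comparisons on the primary outcome, while the stated adjustment is described only for the two contrasts.

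The main consequence is ambiguity. Training lasts 10 weeks (Interventions section), so week 5 falls mid-programme and week 10 at its end. RT could be ahead of control at one visit and not at the other, and the document gives no rule for whether the principal objective has then been met. In an open-label trial that choice should not be left until results are known. A second consequence, conditional on how the gap is filled, is a type I error above 5%.

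**Working it through.** **1. The plan's own figure.** Inputs from the Sample size section: difference 4.25, SD 6, two-sided alpha 0.05, power 0.9.

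n per group = 2(z₀.₉₇₅ + z₀.₉₀)² SD² / difference² = 2 × (1.960 + 1.2816)² × 36 / 18.0625 = 41.9, so 42. The exact t-test calculation gives 42.9, so 43. The stated 39 is not reproduced; 39 to 40 per group gives power of 0.87 to 0.88. That is a separate matter. What counts here is that the calculation describes one test at 0.05, with no second visit and no Dunnett adjustment.

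**2. Critical values.** The unadjusted two-sided 0.05 value is 1.960. For Dunnett with two contrasts sharing RT and equal arms, the contrasts correlate at 0.5. Solving P(|Z₁| ≤ c, |Z₂| ≤ c) = 0.95 gives c = 2.212 (large sample), which is 0.0270 per contrast.

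**3. Error if a win at either visit is accepted.** The documents give no correlation between the week-5 and week-10 changes, so ρ is assumed, with 0.5 to 0.9 as the working range and 0 as the extreme. Under no difference between arms:

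- A: RT versus control and RT versus CT, each at 2.212, at both visits. Error = 1 − P(all four |Z| ≤ 2.212).
- B: RT versus control only, at 1.960, at both visits. Error = 1 − P(|Z₅| ≤ 1.960, |Z₁₀| ≤ 1.960).
- C: RT versus control only, at 2.212, at both visits. Same formula as B with 2.212.

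| ρ | A | B | C |
|---|---|---|---|
| 0 | 0.098 | 0.0975 | 0.053 |
| 0.5 | 0.0915 | 0.0907 | 0.0500 |
| 0.7 | 0.0846 | 0.0835 | 0.0462 |
| 0.9 | 0.0714 | 0.0704 | 0.0389 |

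Check of B at ρ = 0: 1 − 0.95² = 0.0975.

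**4. Error if both visits must be significant.** For RT versus control at 1.960, P(both) = 0.05 + 0.05 − P(either). At ρ = 0.5 this is 0.10 − 0.0907 = 0.0093; at ρ = 0.9 it is 0.10 − 0.0704 = 0.0296. Both are below 0.05.

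**5. What each way of settling it implies for RT versus control** (t-test, difference 4.25, SD 6):

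| Rule | Level | n per group for power 0.9 | Power at 39–40 per group |
|---|---|---|---|
| Week 10 only, 0.05 | 0.05 | 43 | 0.87–0.88 |
| Week 10 only, Dunnett | 0.0270 | 50 | 0.81–0.82 |
| Either visit, Bonferroni over visits | 0.025 | 51 | 0.80–0.81 |
| Either visit, Dunnett and Bonferroni | 0.0132 | 58 | 0.72–0.73 |

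The single-test sample size is closest to one primary visit tested at 0.05.

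**The case against.** A reader might infer that the plan grants two chances to win and therefore does not hold its 0.05 level. The document does not support that as a flat statement, for three reasons.

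- No section says that significance at one visit counts as success. The success rule is missing. If both visits were required, the error would be below 5%.
- The Objective section makes RT versus control the only primary comparison. Read at the Dunnett critical value that the analysis section prescribes, its error over both visits is 3.9% to 5.0% for ρ from 0.9 to 0.5, and reaches 5.3% only at ρ = 0. Excess error arises only if RT versus CT belongs to the same confirmatory family, or if RT versus control is tested at the unadjusted 0.05 of the sample size.
- The text does not say that Dunnett is run separately at each visit, and handling of multiplicity across visits could sit in an analysis plan that is not shown.

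These points stand and limit the error claim. They do not remove the ambiguity. The time point is part of the definition of the primary endpoint, and the article does more than stay silent: it commits to comparisons at both weeks and describes an adjustment that covers arms only.

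**Conclusion.** The point holds as a gap in the definition of the primary endpoint. No visit is named, both are compared on equal terms, and the principal objective has no defined deciding test if they disagree. This conclusion needs no assumption beyond the text.

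The error inflation is conditional. If success at either visit is accepted, it is 7.1% to 9.15% for the two-contrast Dunnett family at each visit, or 7.0% to 9.1% for RT versus control at unadjusted 0.05. RT versus control alone at the Dunnett critical value stays at or below about 5% for ρ of 0.5 or more. These figures rest on normal test statistics, equal arms, a large-sample Dunnett value and an assumed ρ of 0.5 to 0.9.

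Naming the visit leaves one question open: the sample size uses 0.05 without adjustment, while the analysis section prescribes Dunnett.

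**What to change.** State the following in the Outcomes and Statistical analyses sections:

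1. The primary endpoint is change in FMA upper-limb score from baseline to week 10, the end of training.
2. The primary test is the RT minus control contrast at week 10 from the repeated-measures model.
3. All week-5 contrasts are secondary.
4. The level of the week-10 test is either (a) two-sided 0.05, as in the Sample size section, with RT versus CT tested only afterwards as secondary, or (b) the Dunnett-adjusted level, as in the Statistical analyses section, with the sample size stated on that basis.

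The cost is a few sentences, fixed before the results are seen. Visits, data and model do not change. Option (a) matches the level used for the planned size. Option (b) leaves power of 0.81 to 0.82 at 39 to 40 per group, or needs about 50 per group for 0.9.

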### Inclusion and exclusion criteria

Patients will be considered eligible for this study if they are between 20 and 80 years of age, have chronic upper-limb hemiplegia from a supratentorial stroke that occurred at least 6 months before enrollment, are undergoing outpatient or ambulatory rehabilitation, and meet the following functional score requirements: FMA upper-limb scale (9) score of less than 44 points, Stroke Impairment Assessment Set (19) upper-limb distal function score of 1b or above, and modified Ashworth scale (MAS) (20) score of 2 or less.

Patients will be evaluated upon enrollment by their physician, and those with multiple strokes or a cerebellar/brain stem stroke, who have extreme upper-limb pain, or whose upper-limb function is deemed to be improving are not eligible for the study. To avoid complication with other medical conditions, patients with neuromuscular diseases, malignant tumors, balance or gait disturbance, or other serious uncontrolled diseases will be excluded. To ensure patients have the cognitive ability to participate in training and evaluation, patients will be excluded if they have serious aphasia or higher cortical dysfunction (a lack of lucid decision-making ability to participate this study, or a score of 24 points or less on the mini-mental state examination 21). Possible confounding effects of other treatments will be avoided by excluding patients who have received intensive training with an upper-limb training robot or constraint-induced therapy for upper-limb hemiplegia at any time after their stroke, or a botulinum toxin injection within 16 weeks of enrollment. Additionally, before decision-making a participation of study, patients received the standard rehabilitation (physical and occupational therapy) who are not excluded in this study because (1) in study of rehabilitation area for chronic stroke patients, there are few studies that excluse patients receiving the standard rehabilitation before participation of the study from the participant (22–24); (2) in Japan which have health-insurance system that covers all of its citizens, there are few stroke patients in the chronic stroke phase who have not received physical therapy, if they are excluded, the feasibility of this study falls significantly. However, after decision-making a participation of this study, patients were forbidden to receive any other rehabilitation, out of study.

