### Withdrawal from study

Patients will be withdrawn from the study if they undergo certain prohibited therapies after enrolling in the study. These include functional electrical stimulation, transcranial magnetic stimulation, and transcranial direct current stimulation. Training with any other upper-limb rehabilitation robot is also prohibited after informed consent. Patients must not receive botulinum toxin injections during the treatment period.

The investigator can decide to withdraw an enrolled and allocated patient from this study if they have difficulty beginning or continuing study participation, such as failure to attend study visits, withdrawal of informed consent, adverse events or complications, recovery of arm function so that no further rehabilitation is needed, or any other event judged by the investigator to warrant withdrawal. The investigators, after withdrawing a subject, shall perform the planned end-of-study examinations to the extent possible and record the observations, last date of training, and reasons for withdrawal on the case report form.

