### Enrollment and randomization

Subjects who meet all of the inclusion criteria and none of the exclusion criteria, and have given informed consent, will be evaluated by the investigators for enrollment. At enrollment, information will be collected including demographic data, body measurements, stroke information, complications, lifestyle factors, and baseline function measures. The investigator will verify that the patient is eligible to participate and enter information into the electronic data capture and web allocation system as required.

Randomization will be done through the web allocation system. The patients will be randomized to one of the three treatment groups using dynamic allocation by the minimization method based on the baseline FMA upper-limb score, center, period after stroke, and age.

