### Sample size

The principal objective of the study is to verify the superiority of the RT group over the control group in the improvement of FMA upper-limb score. Using the minimal clinically important difference (MCID) as a reference, the mean difference between the patients in the RT and control groups with respect to the FMA upper-limb score is expected to be 4.25 points (30). Given that the subjects in this study will be chronic patients, the deviation is expected to be smaller than that in the pilot study conducted in recovering patients (standard deviation, 8.8) (6), and thus a standard deviation of 6 is expected. Based on a two-sided significance level of 0.05 and a power of 0.9 on Student's *t*-test, a sample size of 39 per group is needed. Considering some loss to follow-up, the sample size was increased from 39 to 40 per group. Additionally, in our similar previous study (6), we recruited 56 case in 6 facilities (about nine case per a facility). Therefore, considering difficulty to recruited case in chronic stage, we judged this study will be feasible to request more than 20 facilities to participate this study.

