For the each of the various measures we will use to assess rehabilitation, the MCID has been established. Of the measures that quantify general hemiplegic arm function, the MCID for FMA is 4.25–7.25 points (30), and that of the ARAT is 10% of the total score (10), or 5.7 points (35). The MCID of MAL, which measures the use of the affected arm in actual life, is 0.5 points for the amount of use scale (36) and 1.0–1.1 points for the quality of movement scale (37). Because clinical resources are limited, there are few interventions/approaches to achieve MCID in the measures of arm function and arm use. However, our pilot studies have shown that combined robot and CIMT therapy could improve arm function and use of the affected arm, and those increases were greater than MCID (38, 39). Those results suggest we will see a promising effect of CT in this ReoGo-J study, and that the combined therapy will overcome the weakness of robotic therapy and significantly increase the use of affected arm in real-life settings.

Currently in Japan, many elderly stroke patients receive one-on-one rehabilitation by physical or occupational therapist 20 min per day at an adult day-care center run by the long-term care insurance system. The protocol of the control group in this study is expected to represent the conventional rehabilitation usually done at such adult day-care center. Therefore, if this study proves RT or CT group exceeded control group, we could suggest a better protocol for rehabilitation for upper extremity hemiparesis for chronic stroke patients at adult day-care center. Furthermore, our suggestion may increase the recovery of upper extremity function and use of affected arm at the same resources and cost as conventional protocol.

However, there are some limitations in this study. For example, there are many factors affecting the prognosis of upper extremity hemiplegia caused by stroke: age, sex, baseline upper extremity motor function, time after stroke, degree of sensory deficit, patients' degree of motivation, family support, various approaches within robotic therapy and CIMT (i.e., types of movement, repetitions, clinical site). In this study, the allocation factor will be set based on previous studies to control for differences in the following characteristics between groups: (1) baseline FMA score (40), (2) time after stroke (41–43), (3) age (43, 44), and (4) clinical site. However, the other factors cannot be controlled by this method.

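### The primary model leaves out three of the four minimisation factors (centre, time after stroke, age); to the extent these are prognostic, the test is conservative and attainable power is forgone

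*Protocol article*

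**What the plan says.** Protocol article, Enrollment and randomization: allocation to the three arms uses "dynamic allocation by the minimization method based on the baseline FMA upper-limb score, center, period after stroke, and age".

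Protocol article, Discussion (limitations): the factors said to affect prognosis include "age, sex, baseline upper extremity motor function, time after stroke, degree of sensory deficit", and clinical site appears later in the same list. The reason given for the allocation factors is that "the allocation factor will be set based on previous studies to control for differences in the following characteristics between groups"; the four that follow are baseline FMA, time after stroke, age and clinical site.

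Protocol article, Statistical analyses: the primary repeated-measures model is specified term by term: "This model will include the group, time point, group-by-time interaction term, baseline FMA upper-limb score, sex, and botulinum toxin injection". The same analysis is to be used for the secondary outcomes. No reason is given for leaving out centre, time after stroke and age.

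On botulinum toxin, the exclusion criteria cover "or a botulinum toxin injection within 16 weeks of enrollment", and the withdrawal section states "Patients must not receive botulinum toxin injections during the treatment period". The analysis section does not say which injections its covariate refers to.

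**The concern.** A factor that is worth balancing at allocation because it predicts outcome is normally carried into the analysis. Minimisation makes the arms alike on the factor, so the treatment estimate varies less than under simple randomisation. A model without the factor does not register that gain: the factor's variance stays in the residual and the standard error is computed as if the arms had not been balanced. The result is a test that rejects too rarely under the null, confidence intervals that are too wide, and less power than the same data could give.

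The article states the model as a definite list of terms, so this is a stated choice and not a detail deferred to a fuller document. The choice is also not consistent, because baseline FMA is both minimised on and adjusted for while the other three factors are not.

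**Working it through.** **Inputs from the protocol article (Sample size).** Difference: "with respect to the FMA upper-limb score is expected to be 4.25 points". Standard deviation 6. Test: "Based on a two-sided significance level of 0.05 and a power of 0.9". 40 patients per arm, 120 in all, and more than 20 facilities to be asked to take part.

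**Assumptions.** The SD of 6 is taken as the residual SD of the model as planned. R² is the share of that variance explained jointly by centre, time after stroke and age. The documents give no value, so a range is shown. Calculations are for RT against control at one time point, two-sided 0.05, without the Dunnett adjustment.

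**The plan's own figure.** n = 2 × 6² × (1.960 + 1.282)² / 4.25² = 41.9, so 42 per group (43 with the exact t distribution) against the stated 39. At 40 per group, power is 88.6% by the normal approximation (87.9% by t). This shortfall is a separate matter; 88.6% serves here only as the starting point at R² = 0.

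**Analytic check, assuming minimisation balances the factors perfectly.**
- Reported SE without the factors: 6 × √(2/40) = 1.342.
- True SE: 1.342 × √(1 − R²).
- Actual alpha: 2 × [1 − Φ(1.96 × reported SE / true SE)].
- Power, factors omitted: Φ((4.25 − 1.96 × 1.342) / true SE).
- Power, factors included: Φ(4.25 / true SE − 1.96).

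At R² = 0.10: true SE = 1.342 × √0.90 = 1.273; power omitted = Φ(1.620/1.273) = Φ(1.273) = 89.9%; power included = Φ(3.339 − 1.960) = Φ(1.379) = 91.6%.

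| R² | Reported SE too large by | Actual alpha | Power, omitted | Power, included |
|---|---|---|---|---|
| 0 | 0% | 0.050 | 88.6% | 88.6% |
| 0.05 | 2.6% | 0.044 | 89.2% | 90.1% |
| 0.10 | 5.4% | 0.039 | 89.9% | 91.6% |
| 0.20 | 11.8% | 0.028 | 91.2% | 94.3% |
| 0.30 | 19.5% | 0.019 | 92.6% | 96.6% |

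**Simulation check.** 120 patients, 20 centres, three arms, minimisation on four factors with the best arm favoured (assumed weight 0.8), a linear model at one time point, and 2,000 runs per scenario. Shares of variance are assumed. The random-centre analysis used the true variance ratio, which slightly flatters it. Monte Carlo error is about 0.5 points for type I error and 0.7 for power.

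| Centre share / age + time share | Omitted: mean SE vs empirical SD (null) | Type I error: omitted / random centre / fixed centre | Power: omitted / random centre / fixed centre |
|---|---|---|---|
| 0 / 0 | 1.336 vs 1.343 | 5.25 / 5.15 / 5.50% | 88.55 / 88.45 / 85.15% |
| 0.05 / 0.05 | 1.339 vs 1.265 | 3.90 / 4.55 / 4.90% | 88.90 / 90.25 / 88.55% |
| 0.10 / 0.10 | 1.338 vs 1.220 | 3.15 / 4.90 / 4.70% | 90.90 / 93.85 / 91.95% |
| 0.15 / 0.15 | 1.339 vs 1.185 | 2.45 / 4.80 / 5.15% | 90.50 / 95.25 / 94.45% |

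Both checks show the same direction and a similar size. The simulation adds one thing: with about 120/20 = 6 patients per centre across three arms, fixed centre effects lose power when the factors do not matter and gain nothing when they matter little.

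**The case against.** The strongest reply has four parts.

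- **The size is assumed.** The documents give no prognostic strength for any of the three factors, and at R² = 0 there is no loss. This stands; the size can only be given as a range.
- **Nothing is lost against the plan.** The sample size rests on a plain t-test, and the power of the analysis without the factors rises with R² (88.6% at 0, 91.2% at 0.20). A reader might infer that the omission pushes the trial below its planned power. The documents do not support that: what is forgone is an available gain, and the shortfall at 40 per group comes from the sample size calculation.
- **The error is on the safe side.** This stands. A reader might infer bias or too many false positives; neither follows from omitting balanced factors in a linear model.
- **The other covariates are defensible.** Sex is listed as prognostic in the Discussion, so adjusting for it is sensible. A reader might also infer that the botulinum toxin term adjusts for something the protocol rules out altogether. It does not: the exclusion covers only the 16 weeks before enrolment and the prohibition only the treatment period. Older injections are permitted, so a history covariate can vary and be valid. What remains is an undefined term, which on its own would be a detail for a fuller document.

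One further defence, that allocation already controls these factors, does not stand. Allocation balances the arms but does not take the factors' variance out of the residual.

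**Conclusion.** The point holds in a conditional form. The listed model omits three of four allocation factors that the protocol itself calls prognostic. Under assumed joint R² of 0.05 to 0.30, the reported standard error is about 3% to 20% too large, actual alpha is about 0.044 to 0.019, and about 1 to 4 points of power are forgone; at R² = 0 there is no effect. The figures rest on an SD of 6, 40 per arm, near-perfect balance, a single time point and no Dunnett adjustment. The repeated-measures model and the adjustment would change the power levels but not the direction. This is a worthwhile efficiency improvement and not a threat to validity.

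**What to change.** Add age and time after stroke (both continuous) and centre (random intercept) to the primary model, keeping baseline FMA and sex, and carry the same terms into the secondary analyses. Centre should not be a fixed effect: more than 20 sites share 120 patients, and in the simulation fixed effects cut power from 88.55% to 85.15% when the factors carried no information.

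As a minor clarification, state that the botulinum toxin covariate is history before randomisation, or drop it, and state that the analysis will not adjust for injections given after allocation, since that is a post-randomisation variable.

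The cost is wording only, because the allocation system already holds all three factors. The downside is a few more parameters, with practically no loss of power if the factors prove uninformative (88.55% against 88.45% in the simulation).

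### The 90% power is stated for one t-test at two-sided 0.05, but the planned Dunnett test of RT vs control has about 82% power at 40 per group on the plan's own inputs

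*Protocol article*

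**What the plan says.** The Objective section ranks the contrasts: "primary objective is to compare the RT and control group, secondary objective is to compare the RT and the CT group". It then places the third one lower: "Additionally, to compare the CT and control group is auxiliary analysis".

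The Sample size section is built on the primary contrast alone, with the FMA total as outcome: "The principal objective of the study is to verify the superiority of the RT group over the control group in the improvement of FMA upper-limb". Its inputs are a mean difference of 4.25 points and a common standard deviation ("thus a standard deviation of 6 is expected"). The error rates are "Based on a two-sided significance level of 0.05 and a power of 0.9", for Student's t-test. It reports 39 per group, raised to 40 for some loss to follow-up. It mentions no multiplicity adjustment.

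The Statistical analyses section plans a mixed model for repeated measures with baseline FMA among its covariates, at an overall level of 0.05. It adds: "For multiplicity adjustment, Dunnett's test will be employed with the RT group used as a reference". With RT as reference, the Dunnett family is RT vs control and RT vs CT. No testing order is stated that would keep the full 0.05 for the primary contrast.

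The Discussion considers what would follow "if this study proves RT or CT group exceeded control group": a better rehabilitation protocol could be suggested for adult day-care centers.

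**The concern.** The article fixes both the test used for sizing and the test used for analysis, and the two have different error rates. Single-step Dunnett treats the primary and secondary contrasts as equals and splits the 0.05 between them. The stated 90% is therefore not the power of the test that will decide the primary question. A reader would take the risk of missing a true 4.25-point benefit to be 10%, when on the plan's own inputs it is nearer 18%.

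A smaller matter is CT vs control. It lies outside a Dunnett family with RT as reference, yet the Discussion speaks of the study proving it.

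**Working it through.** **Inputs.** Difference 4.25, SD 6, two-sided 0.05, power 0.9, and 39 or 40 per group (Sample size section). Three equal groups, with Dunnett against RT (Statistical analyses section). SD 6 is taken as the SD of the analysed quantity.

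**Step 1: the plan's own figure.** Normal approximation: n = 2 × [6 × (1.960 + 1.282) / 4.25]² = 41.9, so 42 per group. With the noncentral t distribution, power is 89.4% at 42 and 90.1% at 43, so the t-test needs 43. The stated 39 does not reproduce. Other readings do not give 39 either (normal approximation): one-sided 0.05 with power 0.90 gives 35, and two-sided 0.05 with power 0.85 gives 36.

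**Step 2: power of the unadjusted t-test.** The noncentrality is 4.25 / (6 × √(2/n)), which is 3.168 at n = 40 and 3.128 at n = 39. With 2n − 2 degrees of freedom, power is 87.9% at 40 and 87.0% at 39. With the three-group error df of 117, it is 88.1% at 40.

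**Step 3: power under Dunnett.** Two contrasts sharing a reference with equal groups have correlation 0.5. Numerical integration with 3n − 3 = 117 df gives a two-sided critical value of 2.239, which is a per-contrast level of 0.0270. The noncentralities are those of step 2.

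| Evaluable per group | t-test at 0.05 | Dunnett |
|---|---|---|
| 36 (10% loss, assumed) | 84.2% | 77.6% |
| 39 | 87.0% | 81.1% |
| 40 | 87.9% | 82.2% |
| 43 | 90.1% | 85.1% |
| 50 | 93.9% | 90.3% |

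Under Dunnett, 49 per group gives 89.7%, so 90% needs 50 evaluable per group.

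**Step 4: splitting the shortfall at 40 per group.** From 90% to 87.9% is 2.1 points, due to the sample size arithmetic. From 87.9% to 82.2% is 5.7 points, due to Dunnett. The total is 7.8 points.

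**Step 5: sensitivity to baseline adjustment (correlations assumed).** If 6 were the unadjusted SD, the residual SD would be 6 × √(1 − r²).

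- r = 0.4: residual SD 5.50, Dunnett 88.7%, t-test 92.7%, gap 4.0 points.
- r = 0.5: residual SD 5.20, Dunnett 92.1%, t-test 95.1%, gap 3.0 points.

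The Dunnett penalty shrinks as the covariate explains more variance, but it does not vanish. In the other direction, the pilot SD of 8.8 quoted in the Sample size section would give Dunnett power of about 47%.

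**Step 6: CT vs control.** A simulation under the global null (2 million draws, 40 per group, one time point) gives a familywise error of 5.0% for the two Dunnett contrasts. Adding CT vs control at an unadjusted 0.05 gives 8.8%.

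**The case against.** Dunnett is a valid procedure. It controls familywise error over exactly the two ranked objectives, and calling one primary and the other secondary does not by itself oblige the trial to test in sequence. That stands: the fault is the disagreement between sizing and analysis, not the choice of Dunnett.

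The planned model also adjusts for baseline FMA, so true power may exceed 82%. That stands in part. The Sample size section gives no correlation, takes no credit for adjustment, and does not say whether SD 6 refers to scores or changes. The 82% is therefore conditional on SD 6, but so is the plan's 90%.

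Three stronger readings are tempting, and the article does not support them.

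- A reader might infer that Dunnett alone took power from 90% to 82%. It did not: about 2 of the 8 points were already lost because 39 per group is too few.
- A reader might infer that the type I error of the ranked comparisons is inflated. It is not: Dunnett holds it at 5%.
- A reader might infer that CT vs control will be tested at an unadjusted 0.05, giving 8.8% familywise error. Nowhere does the article say so. The Objective section calls this contrast auxiliary, and the Discussion sentence is conditional prose, not a testing rule. The 8.8% shows what to avoid; it is not a property of the plan.

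**Conclusion.** The point holds as an inconsistency between the Sample size and Statistical analyses sections. For a 4.25-point difference, SD 6 as the SD of the analysed quantity, and no loss from 40 per group, the planned test of the primary contrast has about 82% power against a stated 90%. Loss to follow-up would lower this; useful baseline adjustment would raise it by an amount the article does not let one compute. The false-positive rate for the two ranked contrasts is sound. The CT vs control issue is minor and calls only for clear labelling. Severity: should be fixed.

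**What to change.** Make the two sections agree, in one of two ways.

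(a) Follow the ranking in the Objective section. Test RT vs control at two-sided 0.05, then RT vs CT at 0.05 only if the first is significant, and drop Dunnett. Restate power as about 88% at 40 per group. The cost is that RT vs CT cannot be claimed if RT vs control fails. Reaching 90% would need 43 evaluable per group (129 in all).

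(b) Keep Dunnett and restate power as about 82% at 40 per group, with the SD assumption written out. This leaves RT vs CT independent of the primary result. Reaching 90% would need 50 evaluable per group (150 in all).

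Under either option, correct the 39 per group, since the stated inputs give 43. State that CT vs control is descriptive, and soften the Discussion's wording about proof so that it does not rest on an unadjusted test. Adding CT vs control as a third step in (a) is possible, but it would then be blocked whenever RT vs CT failed.

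Without a larger sample, both options change wording only. The choice should be made before any comparison of groups is seen.
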